**Figure 2 F2:**
[figure not shown]
Participant timeline and assessments.

#### MT

2.5.2

The MT method of treatment (application of prone stretching, stretching and relaxation, rotation and relaxation in the stretching position, and continuous rotation in the flexion position) is performed. The method (based on treatment techniques such as prone extension, extension release, extension rotation release, and continuous rotation in flexion) is performed for 10 min, Perform 3 sets of each movement, with 15 repetitions per set, maintaining each repetition for 5 s, and allow a 30 s rest interval between sets. It is advisable to ensure that the interval between each action does not exceed 30 min. 40 min of exercise treatment and health lectures are given to the patients to enhance their compliance. A course of 5 sessions/week, combined with health education and a 2-day break between sessions.

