**Methods and analysis:**

A randomized controlled trial will be conducted to compare the efficacy of WQXs with or without MT on patients with chronic low back pain. A total of 74 patients will be randomly assigned to an experimental group (MT and WQXs) and a control group (WQXs). Lumbar range of motion and health-related quality of life in patients with chronic low back pain will be assessed using the range of motion scale, visual analogue scale, and the SF-36 scale. Additionally, surface electromyography (sEMG) and isokinetic muscle strength testing will be employed to evaluate the mechanical properties of the core muscles in the lumbopelvic region. Consider a 20% dropout rate, 74 cases will be gathered in total, taking into account a 20% dropout rate.

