### Design

2.1

All patients are recruited from community residents in the Hongkou and Yangpu districts of Shanghai voluntarily. After obtaining informed consent, they are randomly assigned to either control group or experimental group: control group receive a simplified WQXs intervention, which is refer to as WG, and experimental group receive a combination of simplified WQXs and MT intervention, which is refer to as WMG. The study observation period was 24 weeks. The range of motion (ROM) of the lumbar spine in flexion, extension, and lateral flexion was measured using an electrogoniometer. Pain and the quality of life of patients with chronic low back pain is assessed using scales such as the visual analogue scale (VAS) and the SF-36 questionnaire. The mechanical properties of the lumbago core muscles are evaluated using surface electromyography and isokinetic muscle strength tests to explore the underlying biomechanical mechanisms and enhance clinical efficacy. The following covariates were collected at baseline: age, sex, body mass index (BMI), occupational type (sedentary/manual labor), daily physical activity level, disease duration, and history of low back pain. The impact of these factors on low back pain was analyzed (Figure 1).

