#### WQXs

2.5.1

The movements of tiger play (tiger lift, tiger pounce), deer play (necked deer, necked deer) and bear play (bear shake, bear movement) are selected as the basis for the exercise routine design.

The initial phase consists of a 5-min preparatory warm-up session, followed by a 20-min simplified WQXs exercise targeting the core muscles of the low back and abdomen. Subsequently, the third stage involved a 5-min relaxation training component within the simplified WQXs regimen. In the simplified WQXs training for the core muscles of the lumbar and abdominal regions, a standing and moving position is used, Perform 3 sets of each movement, with 15 repetitions per set, maintaining each repetition for 5 s, and allow a 30 s rest interval between sets. A course of 5 sessions/week, combined with health education and a 2-day break between sessions, The study observation period spanned 24 weeks, comprising a 1-week intervention phase followed by follow-up assessments at weeks 6, 12, 18, and 24 (Figure 2).

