#### Health education

2.5.3

Patients who participate in the project will be told about the background and purpose of the study of MT and WQXs and the principles and functions of MT and WQXs and emphasize the matters that need to be paid attention to in the process of exercise, to help the patients to find the appropriate intensity, frequency and time, and to help the patients to promote the recovery of lumbar spine function safely and effectively through the exercise.

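### Compliance lectures appear only under the MT component, so as written the arms may differ by more than MT; sections 2.5.1 to 2.5.3 need reconciling

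*Protocol article*

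**What the plan says.** The abstract states the comparison as one to "compare the efficacy of WQXs with or without MT on patients with chronic low back pain". Section 2.1 (Design) defines the arms to match: "experimental group receive a combination of simplified WQXs and MT intervention, which is refer to as WMG", whereas WG has the simplified exercise without MT. Neither definition names a lecture or compliance component.

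Section 2.5.1 (WQXs) describes the regimen common to both arms and ends with "A course of 5 sessions/week, combined with health education and a 2-day break between sessions". Section 2.5.2 (MT) attaches health education in the same words. One sentence before that, it adds: "40 min of exercise treatment and health lectures are given to the patients to enhance their compliance". In the intervention sections this is the only mention of lectures and the only measure whose stated purpose is compliance.

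Section 2.5.3 (Health education) is addressed to everyone in the trial: "Patients who participate in the project will be told about the background and purpose of the study of MT and WQXs". It covers the principles of both therapies, precautions, and finding a suitable intensity, frequency and time. It mentions neither lectures nor compliance.

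**The concern.** In an add-on design the background treatment should be the same in both arms. Here the background is WQXs, and its effect depends on how faithfully participants do it. A compliance measure given to one arm only would act on that shared background as well as on MT. WMG participants might then do more WQXs, or do it better, and improve for that reason.

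Such a difference would most plausibly favour the combination. Section 2.9 accepts that therapists and participants know the allocation, and several secondary outcomes are self-reported (VAS, Oswestry, SF-36, and the sleep and depression scales). Blinding the assessor protects the range-of-motion measurement from observer bias. It does not correct a real difference in adherence. At stake is what a positive result could be said to show: MT added to WQXs, or MT and compliance lectures added to WQXs.

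**Working it through.** **1. Which arm does the 40 min sentence describe?** Inputs from section 2.5.1: "The initial phase consists of a 5-min preparatory warm-up session, followed by a 20-min simplified WQXs exercise", then a 5-min relaxation stage. Input from section 2.5.2: MT lasts 10 min.

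- WG session: 5 + 20 + 5 = 30 min.
- WMG session: 30 + 10 = 40 min.

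The plan's 40 min is reproduced exactly as WQXs plus MT. The sentence containing the lectures therefore describes the WMG session, and its reference to the patients most naturally means WMG patients.

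**2. Is the time difference itself a problem?** 40 − 30 = 10 min, and all of it is MT. That belongs to the intended contrast and is not a confounder. The 40 min also leaves no room for lectures, and no lecture duration is given anywhere.

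**3. The three intervention sections side by side.**

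| Section | Who receives it | Health education | Compliance lectures |
|---|---|---|---|
| 2.5.1 WQXs | both arms | yes | not mentioned |
| 2.5.2 MT | WMG only | yes | yes |
| 2.5.3 Health education | all participants | described | not mentioned |

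Read row by row, WG is assigned health education, and WMG is assigned health education and lectures. The stated purposes also differ: compliance for the lectures; information, precautions and choice of a suitable exercise level for the education.

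**4. Does another section settle it?** No. Section 2.1 defines the arms as differing by MT alone, which points towards shared lectures but does not mention them. Sections 2.7 and 3.2.2 speak of staff motivating participants without separating the arms, and again do not mention lectures. The Discussion concedes that the independent effects of the intervention factors are not distinguished, but does not list lectures among those factors.

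**5. Can the effect be sized?** Not from the documents. They give no content, number or length for the lectures, no adherence figures, and no estimate of what better adherence would do to range of motion. The sample-size figures in section 2.10 do not bear on this point.

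**The case against.** The strongest reply is that one-arm delivery is inferred only from where a sentence sits. The sentence does not name the experimental group, and no section withholds lectures from WG. Section 2.1 separates the arms by MT alone, and section 2.5.3 gives education on both therapies to all participants. The lectures may simply be how that education is delivered. The article repeats itself elsewhere: section 2.5.2 lists the MT techniques twice in a row, and the abstract states the dropout allowance twice in one sentence. Naming lectures and then health education could be more of the same.

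This stands as far as it goes: the shared reading is possible. But no section states it, and staff working from 2.5.1 and 2.5.2 as written could give lectures to WMG only. Nor is this detail that a condensed article leaves to a fuller document, because the article does describe the component and places it under one arm's treatment.

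It is also fair to say that much of the article asks about the combined prescription and that the Discussion concedes component effects are not separated. This softens the consequence. It does not remove it, because the stated contrast remains WQXs with or without MT. The primary range-of-motion outcome is instrument-measured by a blinded assessor, so the self-report argument applies only to secondary scales.

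A reader might go further and infer that no gain could be credited to MT, or that the longer WMG session is a second confounder. Neither follows. Even if only WMG had lectures, part of a gain could still be due to MT, and the extra 10 min are the treatment under test.

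**Conclusion.** The point holds as an unresolved inconsistency, not as an established confounder. As written, compliance lectures belong to the MT section alone, alongside the health education both arms receive, and nothing equates the two or gives the lectures to WG. If the text is followed literally, a difference between arms reflects MT plus a compliance measure and could not be credited to MT alone. If the lectures are the shared education under another name, the comparison is intact and only the wording is at fault.

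No size can be attached. One could posit a lecture effect and compute how often the trial would then reach significance with MT inert, but that would show only what any bias of that size does. It would not be evidence that one exists here. The conclusion rests on the placement of the sentence, on the match of its 40 min to the WMG session, and on the silence of 2.5.1 and 2.5.3. It is best treated as a cheap improvement, worth making under either reading.

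**What to change.** Reconcile sections 2.5.1 to 2.5.3. Move the lecture part of the sentence from 2.5.2 to 2.5.3, say whether lectures and health education are the same thing, and state that lectures and compliance support are delivered in the same form and amount to both arms. Leave the exercise components as they are.

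If lectures have already been given to WMG only, word the conclusion as the effect of MT plus lectures added to WQXs.

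If both arms already receive the lectures, the change is to wording only. If not, the cost is slightly more session time for WG, and possibly a smaller observed difference if lectures would have contributed to it.

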#### Health education

2.5.3

Patients who participate in the project will be told about the background and purpose of the study of MT and WQXs and the principles and functions of MT and WQXs and emphasize the matters that need to be paid attention to in the process of exercise, to help the patients to find the appropriate intensity, frequency and time, and to help the patients to promote the recovery of lumbar spine function safely and effectively through the exercise.

### Outcome measures

2.6

During the cycle, participants will undergo an initial assessment at baseline within one week of enrollment, followed by follow-up evaluations at four time points: 0 weeks, 6 weeks, 12 weeks, and 24 weeks. The primary outcome is lumbar lordosis mobility. Secondary outcomes include surface EMG, isometrics muscle strength, the Depression Self-Rating Scale, theVAS score, score of the JOA Lower Back Pain Rating Scale, score of the Oswestry Lumbar Functional Index Questionnaire, score of the SF-36 Healthy Quality of Life Scale, and score of the Pittsburgh Sleep Quality Inventory (PSOI).

### Facilitator selection, training and supervision

2.7

The following tight controls are placed on the quality of each stage of the study's implementation to guarantee the trial's safety, rigor, and scientific validity:
Patient inclusion: Patients are screened in compliance with the study's diagnostic, inclusion, and exclusion criteria.Sample size determination, group allocation, randomization, blinding procedures, and statistical methods are established based on a comprehensive review of relevant literature.Before the pilot study is carried out, the study's personnel receive rigorous training.WQXs train teachers perform WQXs imagery training and provide rich and efficient WQXs demonstrations to guarantee the quality of the motions. Primary therapists conduct comprehensive rehabilitation training and assessments.Bedside physicians and rehabilitation therapists work collaboratively to actively engage participants, clearly explaining the purpose and procedures of the motor imagery intervention until full implementation is achieved.

### Patient and public involvement

2.8

This preliminary investigation will enroll a diverse group of individuals with chronic low back pain, recruited from the Hongkou and Yangpu districts in Shanghai. All interventions provided for these participants will take place in their respective local communities. The trial will be coordinated and supervised by the Fourth People's Hospital of Tongji University, based in Shanghai, which will also be responsible for managing the trial data.

### Blinding

2.9

Random allocation will be assigned by an independent person who will not involved in the trial. As this study is an exercise intervention, it will be difficult to conceal the grouping from the therapists and subjects, but it will be possible to blind the outcome measures. A new assessor will be assigned to replace the assessor familiar with the allocation in order to realize single blinding.

### Sample size

2.10

In this study, the formula for calculating the sample size for the two-sample test of variance was used, with lumbar anterior flexion range of motion as the main effector, and referring to the literature report and the result of the pre-test, the range of motion of lumbar anterior flexion in the two treatment groups was 46.20 ± 5.25 and 42.59 ± 5.14 (26), respectively, which was calculated to require 33 patients in each group. Accounting for an anticipated 10% dropout rate, the total sample size needed is 74 participants.

### Statistical analysis plan

2.11

According to the Case report form (CRF) table, after each measurement, the data are double-entered into Stata software within one week, and the data are processed and analyzed using SPSS26.0 statistical software. Measurement data are expressed as mean ± standard deviation, and the *t*-test is used if the data meet the normal distribution, and the rank-sum test is used if the data do not meet the normal distribution and the chi-square test was used for comparison of count data. *α* = 0.05 was used as the test level for significant differences.

If there are intolerable or serious adverse reactions during exercise, the trial will be discontinued; however, those who have participated in more than 1 cycle of exercise should be counted for efficacy. Volunteers who are unwilling to continue the clinical trial during the trial and take the initiative to ask the investigator to discontinue the trial could discontinue the trial. In case of discontinuation, more than 1/2 of the data are analyzed and less than 1/2 are excluded.

If imbalances exist between the two groups at baseline regarding variables such as gender, occupation, and physical activity, Analysis of Covariance (ANCOVA) with covariate adjustment will be employed as a sensitivity analysis。

Recognizing that age may influence musculoskeletal elasticity, the speed of rehabilitation response, and compliance, we performed a stratified analysis by age (e.g., <40 years vs. ≥40 years) in addition to conventional analyses, to examine whether there was a significant interaction effect of the intervention across different age groups.

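### Section 2.11 words stopping for an adverse reaction like voluntary withdrawal, so it reads most naturally as leaving the trial and its later assessments

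*Protocol article*

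**What the plan says.** The second paragraph of section 2.11 (Statistical analysis plan) makes four statements in sequence.

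- On harm: "If there are intolerable or serious adverse reactions during exercise, the trial will be discontinued".
- In the same sentence, as a qualification: "those who have participated in more than 1 cycle of exercise should be counted for efficacy".
- On volunteers who no longer wish to continue: those who "take the initiative to ask the investigator to discontinue the trial could discontinue the trial".
- On the data of people who discontinue: "In case of discontinuation, more than 1/2 of the data are analyzed and less than 1/2 are excluded". This sentence does not distinguish reasons for discontinuation.

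No other section separates stopping the exercise from leaving the study, and none says that a participant stopped for harm remains in follow-up.

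**The concern.** Stopping treatment and leaving the study are different events. A participant who must stop exercising because of a reaction can normally still be measured. Section 2.11 names the trial, not the exercise, as what is discontinued, and uses the same expression for a volunteer who withdraws.

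The distinction matters here because the arms differ in treatment burden. Under section 2.1 the "experimental group receive a combination of simplified WQXs and MT intervention", while controls receive Wuqinxi alone. Section 2.9 accepts that therapists and participants will know the allocation. Exits for reactions could therefore be more frequent in one arm and be related to how the participant would have done. Section 2.9 also plans blinded outcome assessment, but that protects only measurements that are taken. An outcome not collected at its visit cannot be recovered by later analysis.

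**Working it through.** The plan gives no figure on this point, and the sample size plays no part in it. The check is a reading of the text followed by a count of visits.

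**1. The wording.** The harm sentence and the withdrawal sentence share verb and object and differ only in voice. The withdrawal sentence plainly concerns one volunteer. Read alongside it, the harm sentence most naturally concerns one participant too. The qualification about people with more than one cycle supports this, because it treats participants individually.

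**2. The data rule.** Sorting discontinued people by the share of data they hold makes sense if data stop accruing at exit. This suggests that later visits are not made, but it does not state it. The rule may also have been meant mainly for voluntary withdrawal, which it directly follows.

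**3. The efficacy clause.** The article does not define a cycle. Assume it is one weekly course, from section 2.5.2: "A course of 5 sessions/week, combined with health education and a 2-day break between sessions".

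- If exercise runs beyond week 1 (a second assumption), someone stopped after more than one cycle but before week 6 holds no post-baseline assessment. That person can contribute to efficacy only if measured after stopping. The clause then works only if visits continue, and the discontinuation wording does not provide for that.
- If section 2.5.1 is taken as written, with the period "comprising a 1-week intervention phase followed by follow-up assessments at weeks 6, 12, 18, and 24", nobody can exceed one cycle and the clause retains no one.

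**4. Visits at stake per stopped participant, if collection ends at exit.** Section 2.5.1 gives weeks 6, 12, 18 and 24, which is 4 post-baseline visits. Section 2.6 gives "follow-up evaluations at four time points: 0 weeks, 6 weeks, 12 weeks, and 24 weeks"; taking week 0 as baseline leaves weeks 6, 12 and 24, which is 3. The number at stake is the count of scheduled visits later than the exit.

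| Exit | Section 2.5.1 schedule | Section 2.6 schedule |
|---|---|---|
| before week 6 | 4 of 4 | 3 of 3 |
| weeks 6 to 12 | 3 of 4 | 2 of 3 |
| weeks 12 to 18 | 2 of 4 | 1 of 3 |
| weeks 18 to 24 | 1 of 4 | 1 of 3 |

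Under the one-week intervention phase of section 2.5.1, any reaction during exercise falls before week 6, so only the first row applies. The other rows need the assumption that exercise lasts longer.

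**5. What cannot be computed.** The article gives no reaction rate, no split by arm and no outcome difference between those who stop and those who continue. No bias in degrees of motion can be derived.

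**The case against.** The strongest reply is that the article never says assessments end after a reaction. What remains could be called silence on follow-up after stopping, which a condensed article may leave to the full protocol. The English is loose throughout, so the repeated expression may simply be imprecise wording for stopping the exercise. The clause nearest to the harm rule favours keeping people in the analysis, and a reader could infer from it that visits continue. The illustration built on that clause needs two assumptions: a one-week cycle, and exercise lasting beyond the one week stated in section 2.5.1. Finally, nothing in the article suggests that such reactions will be common.

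Much of this stands. The end of visits is an inference, the cycle illustration is conditional, and no magnitude can be shown. The silence argument does not dispose of the point, however. The article states a rule for this event, and that rule names the trial as what stops. Someone applying it as written would have no reason to keep the participant in follow-up.

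Two stronger readings are tempting. A reader might infer that the plan ends data collection after harm and so biases the comparison; the text does not state the first part and gives nothing from which to show the second. A reader might also infer that one reaction halts the whole study. The literal words allow that, but the neighbouring sentences about individual participants make it the less natural reading.

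**Conclusion.** The point holds as a fault of wording with a plausible consequence for data collection. Section 2.11 does not distinguish stopping exercise for harm from leaving the trial, and it most naturally reads as the latter. If it is followed that way, between one and all of the post-baseline visits are lost for each participant stopped, and all of them under the one-week phase of section 2.5.1. The loss could be related to arm and outcome because McKenzie therapy is in one arm only and allocation is open. This rests on two inferences: that the harm rule applies to the individual, and that collection ends at exit. The effect on the treatment comparison cannot be sized. It is a cheap improvement, with medium confidence in the reading and less confidence that data will actually be lost.

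**What to change.** Reword the harm rule in section 2.11 along these lines: *If a participant has an intolerable or serious adverse reaction, that participant's exercise is stopped; the participant stays in all scheduled assessments to week 24 unless consent is withdrawn, and these data are analysed in the randomised group regardless of the number of cycles completed.*

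Reserve the expression about discontinuing the trial for withdrawal of consent, and make clear that the half-of-data condition does not remove participants whose exercise was stopped for harm. State any study-level halt in a sentence of its own. The clinical threshold for stopping is for the sponsor to set.

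The cost is a short wording amendment and some effort to keep stopped participants attending; no new visits or staff are needed. The benefit is limited to participants not yet past week 24. Section 2.3 has enrolment starting in September 2023 and the article is dated May 2026, so how many remain in follow-up is not known from the document.

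### The stated discontinuation rule drops randomised participants by how much data they supplied, with undefined thresholds, and leaves the efficacy comparison open to attrition bias of unknown direction

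*Protocol article*

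**What the plan says.** Section 2.11 (Statistical analysis plan) sets two conditions for counting a participant who stops early.

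- For stops caused by intolerable or serious adverse reactions, the test is exercise exposure: "those who have participated in more than 1 cycle of exercise should be counted for efficacy".
- The text then allows voluntary withdrawal ("Volunteers who are unwilling to continue the clinical trial during the trial and take the initiative to ask the investigator to discontinue the trial") and follows it with a rule based on the amount of data: "In case of discontinuation, more than 1/2 of the data are analyzed and less than 1/2 are excluded".

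Neither *cycle* nor half of the data is defined. Two other places bear on *cycle*. Section 2.5.1 (WQXs) describes a weekly unit, "A course of 5 sessions/week, combined with health education and a 2-day break between sessions", and then says "The study observation period spanned 24 weeks, comprising a 1-week intervention phase followed by follow-up assessments at weeks 6, 12, 18, and 24". Section 2.6 (Outcome measures) uses the word for the assessment period: "During the cycle, participants will undergo an initial assessment at baseline within one week of enrollment".

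The only sensitivity analysis named in section 2.11 is ANCOVA for baseline imbalance. Section 2.9 accepts that therapists and participants will know the allocation and plans to blind outcome assessment.

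**The concern.** Randomisation makes the two arms comparable as randomised. Once participants are removed for stopping early, the people compared are those who stayed long enough, and staying can depend on the arm. Here the experimental arm has McKenzie therapy added to the Wuqinxi exercise, everyone knows their allocation, and adverse reactions during exercise are one named reason for stopping. Lack of benefit is another plausible reason, and it could act in either arm. If those removed would have done worse or better than those kept, and this differs between arms, the estimated difference is biased. Blinded assessors do not prevent this, because the problem is who is measured and counted, not how they are measured.

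The undefined terms add a second problem. If it is unclear who meets the threshold, membership of the analysis set may have to be settled once outcomes are known.

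**Working it through.** **1. The plan's own figure.** Section 2.10 gives flexion range of motion as follows: "in the two treatment groups was 46.20 ± 5.25 and 42.59 ± 5.14".

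- Difference: 46.20 − 42.59 = 3.61 (taken as degrees).
- Pooled SD: √((5.25² + 5.14²)/2) = 5.195. Standardised difference: 3.61/5.195 = 0.695.
- Two-sided α = 0.05. Section 2.11 gives the level ("0.05 was used as the test level for significant differences"); two-sidedness and 80% power are my assumptions, and they reproduce the plan's number.
- n = 2(1.960 + 0.842)²/0.695² ≈ 32.5, so 33 per group. This matches the plan.
- 66/(1 − 0.10) = 73.3, so 74 in total, or 37 per arm. This also matches.

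**2. The two rules side by side.**

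| Participant | Exposure rule | Half-data rule |
|---|---|---|
| Stops for adverse reaction, more than 1 cycle, less than half of the data | counted | excluded, if the rule applies to every discontinuation |
| Withdraws voluntarily, less than half of the data | not addressed | excluded |
| Stops with exactly half of the data | depends on reason and cycles | not covered |

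Exactly half is a realistic case. Sections 2.5.1 and 2.6 each list four follow-up time points (though not the same four), so if data are counted by visit, two of four is exactly half.

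**3. What *cycle* could mean.** If it is the weekly course, the 1-week intervention phase in section 2.5.1 leaves nobody with more than 1 cycle, and the exposure rule never applies. If it is the whole assessment period, as in section 2.6, an early stopper cannot have completed more than one. These passages must be reconciled.

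**4. Illustration of bias.** The document gives no outcome data on discontinuers, so these values are assumed: one arm alone excludes a share q of its 37 participants, and those excluded would have scored g SDs below those retained. The shares 10% and 20% are the dropout rates in section 2.10 and the abstract; placing all of the loss in one arm is an assumption.

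- Full-arm mean = retained mean − q·g·SD, so the shift in the estimate is q·g·5.195.
- SE = 5.195·√(1/(37(1 − q)) + 1/37), with the other arm kept at 37.
- Type I error = P(|Z + shift/SE| > 1.96).

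| q | g | Shift (degrees) | Share of 3.61 | SE | Type I error |
|---|---|---|---|---|---|
| 10% | 0.5 | 0.26 | 7% | 1.241 | 5.5% |
| 10% | 1.0 | 0.52 | 14% | 1.241 | 7.0% |
| 20% | 0.5 | 0.52 | 14% | 1.281 | 6.9% |
| 20% | 1.0 | 1.04 | 29% | 1.281 | 12.8% |

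The shift favours the arm that loses its poorer performers. If the control arm loses them instead, the sign reverses. If both arms have the same gap, the shift is (q₁ − q₀)·g·SD, which is zero when the rates are equal. For 20% against 10% it is 0.26 (g = 0.5) or 0.52 (g = 1).

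**The case against.** Several points on the other side carry weight.

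**The rules may not conflict.** The half-data sentence comes directly after the one on voluntary withdrawal, so it can be read as one rule for adverse-reaction stops and another for withdrawals. A reader might infer a certain contradiction, but the text does not establish one. However, its opening words cover discontinuation without restriction, so overlap is possible. Even on the separate-rules reading, inclusion depends on the reason for stopping, and randomised participants are still dropped.

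**The article is condensed.** A reader might also infer that the trial has no intention-to-treat analysis. A full plan may exist, and silence here is not evidence against it. The point rests only on the exclusion that the article states.

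**The illustration is one-sided.** It places all loss in one arm and makes those lost do worse. Nothing in the document supports either assumption. Unblinded controls could leave for lack of benefit, which would reverse the sign. The 20% case is extreme: 0.20 × 37 = 7.4 exclusions in one arm equals the 10% allowance for the whole trial (0.10 × 74 = 7.4). A reading that the rule favours the combined treatment is therefore not supported.

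**The difference in burden is modest.** The addition described is 10 minutes of McKenzie therapy to a 30-minute session (5 + 20 + 5). This weakens the expectation of a large difference in stopping but does not remove it.

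**Conclusion.** The point holds for the stated exclusion. Section 2.11 conditions the efficacy comparison on a post-randomisation event in a trial where participants know their arm, and the thresholds are too loosely worded to fix the analysis set in advance. Confidence is high on the exclusion rule and its undefined terms. The conflict between the two rules is possible, not certain.

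The direction and size of bias are unknown. The table shows what the rule could allow under one-arm loss; it is not a forecast, and its range must be read with zero and the mirror-image values included. The matter should still be settled before analysis, because the rule decides whose data enter the efficacy comparison and the named sensitivity analysis does not address attrition.

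**What to change.** Make these changes in section 2.11:

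1. Define the primary analysis as all randomised participants in their assigned arm, using every range-of-motion value obtained.
2. Continue the scheduled assessments after the intervention stops, for those who still consent. Some who withdraw will decline all follow-up, so missing values will remain.
3. Handle missing values with a mixed model or multiple imputation. Add a missing-not-at-random sensitivity analysis, for example delta-adjusted. A missing-at-random method alone does not remove bias from unobserved differences, and it gains little from a participant with only a baseline value.
4. Keep one threshold, exposure or amount of data, only for a labelled per-protocol sensitivity analysis. Define its terms, cover the case of exactly half, and apply it whatever the reason for stopping.
5. Reconcile the meaning of *cycle* with the length of the intervention phase in section 2.5.1 and the use of the word in section 2.6.

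The cost is protocol wording, modest extra analysis, and the already scheduled assessments for participants who stop exercising but agree to be followed. No additional participants are needed.
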